#### Secondary

Secondary clinical outcome measures will be assessed in a blinded fashion by the Clinical Events Review Committee. These outcomes will be measured in hospital, at routine 6-week clinical follow-up and from telephone questionnaires. Outcomes are as follows:-

##### a. Cause-specific death

• Death will be classified into cardiac, other vascular and non-cardiovascular, where possible, using autopsy reports and death certificates. Death will also be classified by ICD code.

• ***Death due to cardiac causes: ****Cardiac causes of death such as congestive heart failure, arrhythmia or myocardial infarction*.

• ***Other vascular causes of death: ****Vascular causes of death such as pulmonary embolus, dissection, cerebrovascular accident or bleeding event*.

• ***Non-cardiovascular causes of death: ****This includes any other cause of death*.

##### b. 30 day mortality

• Death from any cause by 30 days post surgery

• Cause-specific death by 30 days post surgery

##### c. 90 day mortality

• Death from any cause by 90 days post surgery

• Cause-specific death by 90 days post surgery

##### d. Need for re-intervention

ie percutaneous coronary intervention or redo surgery

##### e. Other clinical events

• Myocardial infarction, major bleeding, cerebrovascular accident and other serious adverse events will be captured.

##### f. Quality of Life and cost effectiveness evaluation

• These outcomes will be measured from questionnaires (Rose -shortened form, EuroQol-5D, SF36 and Health Services Resource use). These outcomes will be assessed blind to the knowledge of which arm the trial the patient is in.

### Follow-up

A summary of the follow up is shown in Table 1.

**Table 1 T1:** Follow-up schedule

	**Pre-op**	**Intra-op**	**Pre-discharge**	**6 wk clinic visit (± 1 m)**	**Annual telephone and postal follow up for 10 years (± 1 m)**
***Baseline characteristics***	***√ ***				
***Clinical history***	***√ ***				
***Physical exam***	***√ ***			***√ ***	
***Medications***	***√ ***		***√ ***	***√ ***	***√ ***
***LV function assessment***	***√ ***				
***Quality of Life assessment ***	***√ ***				***√ ***
***Health Service Resource use***		***√ ***	***√ ***	***√ ***	***√ ***
***Operation details***		***√ ***			
***Clinical Outcomes***			***√ ***	***√ ***	***√ ***

Annual Quality of Life questionnaires (Table 2) will be sent to study participants by post, no clinic visits are required apart from the routine clinical 6-week post operative visit. Participants will be sent stamped addressed envelopes to improve the return rates of postal questionnaires. Study co-ordinators will telephone participants to alert them to the questionnaires arrival and to ask them about medications, adverse events and health services resource use.

**Table 2 T2:** Quality of Life questionnaires

**Questionnaire**	**Information collected**	**YEAR**										
		
		Pre-op	1	2	3	4	5	6	7	8	9	10
Rose (shortened form)	Simple, evaluates angina	+	+	+	+	+	+	+	+	+	+	+
EuroQuol-5D	Short and simple, for economic evaluation	+	+	+	+	+	+	+	+	+	+	+
SF-36	Detailed, examines eight separate dimensions	+					+					+

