Angiographic studies demonstrate markedly superior patency of BIMA grafts, compared to vein grafts, refuting the assertion that the superior patency of IMA grafts is due to better 'run-off' in the LAD territory. Patency rates for BIMA to various coronary arteries, are 98% at 7 days [14] and 95% at two [20] and seven years [21]. Furthermore, off-pump CABG (OPCAB) now makes CABG feasible in patients whose advanced age previously precluded CABG using cardiopulmonary bypass. A composite radial artery from one or both IMA, allows up to four grafts as an 'off-pump' CABG, eliminating both cardiopulmonary bypass and aortic manipulation and minimizing the risk of cerebral injury [22].

Opposition to BIMA grafting is largely based on the perception of increased perioperative risk and especially sternal wound morbidity. There is consistent evidence, however, that the operative mortality of BIMA grafting at 1%–2% [12,13] is no higher, and may, in fact, be less than that of the standard operation because of a reduced risk of early graft failure.

Sternal dehiscence is a potential complication of BIMA grafts and particularly in diabetics. In reality, there is only a minimal increase in the risk of impaired wound healing in both non-diabetics [13,23-27] and diabetics [23-27] unless the patient is morbidly obese and/or has marked respiratory impairment [24]. The risk of impaired wound healing can be minimized with judicious patient selection and modification of the IMA harvesting method whereby a 'skeletonized' rather than 'pedicled' fashion preserves collaterals and sternal blood supply [25] and improves wound healing, particularly in diabetics. No difference has been found in myocardial enzymes [28], parameters of respiratory exchange [29] or in respiratory injury between SIMA and BIMA patients. BIMA harvesting adds around 30 minutes to a three-hour operation.

Uncertainty remains because there is no randomised evidence, therefore a randomised trial – the Arterial Revascularisation Trial (ART) – has been designed to compare SIMA versus BIMA grafting in coronary revascularisation. ART will compare survival rates, need for redo CABG, other clinical events, quality of life and cost effectiveness of SIMA versus BIMA grafting.

The main objective of ART is to assess whether the use of both IMA during CABG (BIMA) improves survival and reduces the need for further interventions over that observed with a single IMA (SIMA).

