#### Analyses of cost-effectiveness and quality of life data

Overall analysis will be performed from the perspective of the health care system; basic information will also be collected on employment status during follow-up from the annual Health Service Resource use questionnaire. Unit costs obtained from centres and from national sources will be used to obtain a cost per patient. Missing data will be handled via multiple imputations in statistical analyses.

In line with the primary outcome of the trial, the main outcome measure in the cost-effectiveness analysis will be life years gained. These will be estimated within-trial and over the patients' lifetime, by taking the sum of life years obtained in each arm of the trial within the follow-up period and modelling subsequent life expectancy, using different assumptions about any within-trial treatment effects continuing. The cost per quality adjusted life year (QALY) will be calculated in the same way, using results from the EQ-5D annual questionnaires.

The cost-effectiveness analysis will be reported in terms of the incremental cost per life year and the incremental cost per QALY gained. All resource use, cost, outcome and cost-effectiveness information will be reported as the mean per patient in each arm of the trial and the mean difference, with appropriate measures of variance. Cost-effectiveness in sub-groups will be estimated by applying any overall relative risk reduction and cost reduction to different baseline absolute risk groups. Cost-effectiveness acceptability curves and net benefit statistics will also be reported.

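### EQ-5D is not collected between the pre-operative assessment and year 1, so an early quality-of-life difference between SIMA and BIMA that resolves within the year cannot be detected

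*Protocol article*

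**What the plan says.** - **Schedule.** In the Follow-up section, Table 1 ticks quality of life before surgery and at the annual contacts only. Table 2 agrees: Rose and EQ-5D before surgery and at years 1 to 10, SF-36 before surgery and at years 5 and 10. The text says "Annual Quality of Life questionnaires (Table 2) will be sent to study participants by post".
- **The 6-week visit.** The same section says that "no clinic visits are required apart from the routine clinical 6-week post operative visit". Table 1 ticks that visit (± 1 month) for physical examination, medications, resource use and clinical outcomes, but not for quality of life.
- **QALYs.** In the section on cost-effectiveness and quality-of-life analyses, the cost per QALY is obtained "using results from the EQ-5D annual questionnaires". QALYs are not the leading measure there: "the main outcome measure in the cost-effectiveness analysis will be life years gained".
- **The disputed harm.** The Background says: "Opposition to BIMA grafting is largely based on the perception of increased perioperative risk and especially sternal wound morbidity". It answers that "there is only a minimal increase in the risk of impaired wound healing", with an exception for morbid obesity or marked respiratory impairment, and gives no rates.

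**The concern.** The argument against BIMA that the protocol sets out to test concerns the first weeks after surgery. The Background also says that earlier evidence on adverse consequences was very limited. The schedule takes no quality-of-life measurement in that period, so the trial cannot say whether early recovery differs between the arms, in either direction.

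Costs and utilities are also treated unevenly. Table 1 and the section on health service research issues record theatre time, ward days and treatment of complications, so the costs of an early complication enter the cost-effectiveness ratio. A utility loss that has resolved by year 1 does not. No analysis plan written later can recover a measurement that was not taken; it could only bring in utility values from outside the trial.

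**Working it through.** **1. What the schedule can see.** Randomisation makes the arms equal before surgery in expectation. If mean EQ-5D is also equal at year 1, any method that uses only those two values gives survivors in both arms the same first-year utility. The measured contribution of a transient difference is then 0, whatever its true size.

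**2. The plan's own figure.** The protocol gives no figure for quality of life or QALYs, so its planned mortality effect is the yardstick. Inputs from Trial size: 25% against 20% at 10 years, 90% power, 5% alpha (taken as two-sided), 1:1 allocation.

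n per arm = [1.960 × √(2 × 0.225 × 0.775) + 1.282 × √(0.25 × 0.75 + 0.20 × 0.80)]² / 0.05² = 1464, or 2928 in total. The stated number reproduces. A 6-week EQ-5D does not change it.

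**3. Planned gain within 10 years.** Assume exponential survival with rate λ = −ln S(10)/10, so that life years = (1 − S(10))/λ.
- SIMA, S(10) = 0.75: 8.690 years.
- BIMA, S(10) = 0.80: 8.963 years.
- Gain: 0.273 life years, or 0.273 × 0.8 = 0.218 QALY at an assumed utility of 0.8.
- If the same 10-year difference arises only from year 5, the gain is 0.130 life years (× 0.8 = 0.104 QALY); only from year 7, 0.076 (× 0.8 = 0.061 QALY).

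**4. Size of the omitted loss.** Loss per BIMA patient = excess complication risk × utility loss × months/12. All three inputs are assumptions.

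| Excess risk | Utility loss | Months | QALY omitted |
|---|---|---|---|
| 1% | 0.1 | 1.5 | 0.00013 |
| 2% | 0.3 | 3 | 0.0015 |
| 5% | 0.3 | 6 | 0.0075 |

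Against the planned gain, the upper end is 0.0075/0.218 = 3.4% under proportional hazards, 0.0075/0.104 = 7% for benefit from year 5, and 0.0075/0.061 = 12% for benefit from year 7. The lower end is 0.00013/0.218, about 0.1%.

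**5. What a single 6-week value would do in the QALYs.** Let d be the arm difference at 6 weeks, with none before surgery or at year 1.
- Straight lines through pre-op, 6 weeks and year 1: (6/52) × d/2 + (46/52) × d/2 = 0.5d.
- A constant loss d lasting 6 weeks: (6/52) × d = 0.115d. Lasting 12 weeks: (12/52) × d = 0.231d.
- Overstatement by the straight line: 0.5/0.231 = 2.2-fold to 0.5/0.115 = 4.3-fold.
- If the difference is instead taken to return to zero at 12 weeks: (12/52) × d/2 = 0.115d.

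The two calculations together span the 6- to 12-week losses; the straight line alone does not.

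**The case against.** The strongest reply is that the schedule is internally consistent and suits a 10-year question. Neither survival nor life years gained uses EQ-5D, so one more time point would serve a secondary measure only. That stands, and it limits the weight of the point.

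Three stronger readings are tempting, and the documents do not support them.

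- **That the early period contributes nothing to the QALYs.** Early deaths still remove life years, and 30- and 90-day mortality are outcomes. Harm that persists to year 1 lowers the year-1 EQ-5D. Early clinical events are recorded in hospital and at 6 weeks. Only a transient utility difference is lost.
- **That the QALYs are biased toward BIMA.** This needs a net early decrement with BIMA. The Background calls the wound excess minimal and suggests that early graft failure may be less frequent with BIMA; an early benefit of that kind would be missed as well.
- **That the omission could reach about 30% of the gain.** That figure takes a mean deficit of 0.10 in every BIMA patient for 12 weeks (0.10 × 12/52 = 0.023 QALY) and divides it by the smallest survival gain, 0.076, which is in life years. At a utility loss of 0.3 per complication, a mean deficit of 0.10 implies an excess complication rate of 0.10/0.3 = 33%, which does not fit the protocol's description.

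It is also fair to say that the article does not state how utilities are interpolated and does not rule out event-based decrements. These may stand in an economic analysis plan that is not shown. They would soften the effect on QALYs, but would not supply an early quality-of-life comparison.

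**Conclusion.** The point holds as a minor design gap. EQ-5D is printed at no time between the pre-operative assessment and year 1, a suitable visit exists in that interval, and a transient early difference cannot be detected without it. If there is a net early decrement with BIMA, the QALYs could modestly favour BIMA; the documents settle neither the direction nor the size.

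Under the assumed event-based ranges the effect is at most about 3% of the planned within-trial gain with proportional hazards. It reaches about 12% only if the whole survival benefit arises after year 7, and it would weigh more if survival turned out nearly equal. These percentages rest on assumed complication rates, utility losses and durations, on exponential control survival and on a utility of 0.8. The primary outcome, the sample size and the main cost-effectiveness outcome are unaffected.

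**What to change.** - Add EQ-5D to the 6-week visit column of Tables 1 and 2. Table 2 itself describes the instrument as "Short and simple, for economic evaluation".
- Record the date of completion. A window of ± 1 month around week 6 runs from about week 2 to week 10, when recovery may be changing quickly.
- Report the 6-week EQ-5D difference between the arms as a secondary quality-of-life result.
- Use the 6-week value in the QALY calculation, but do not rely only on a straight line from 6 weeks to year 1. Add a sensitivity analysis in which the difference resolves earlier, for example by 12 weeks.

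The cost is one short questionnaire at a visit that already takes place, with no new visit, staff or procedure. The drawbacks are a small added burden for patients and some missing 6-week forms.

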### Health service research issues

Information will be collected in each centre on resources used during the hospital stay, time in operating theatre, total blood and coagulant product use, time in cardiac recovery unit, days on ward; treatment of complications (eg return to theatre), drugs prescribed at hospital discharge, use of cardiac rehabilitation.

Information on subsequent in-patient episodes (including interventions and duration) on outpatient visits and diagnostic procedures, and on general practitioner and practice nurse consultations will be obtained from the patient during the annual telephone call. This call will also ask about specified medications (eg aspirin, statins, ace-inhibitors, beta-blockers, calcium channel antagonists). Participating centres will also record and report subsequent rehospitalisations and revascularisations of patients in the trial.

### Trial size

#### Number of patients

To achieve an absolute 5% reduction in 10-year mortality (ie from 25% to 20%), with 90% power at 5% alpha requires 2928 patients. The mortality data is taken from a summary of previous studies published in reference 12.

The aim is to enrol at least 3000 patients (1500 in each arm) over a 2 to 3 year recruitment period in 20 centres in the UK, Australia, Poland and Brazil (Table 3). As the intervention is the operation, compliance is likely to be 100% except in the unusual situation where the planned operation is not possible for technical reasons.

**Table 3 T3:** ART Principal Investigators and centres

#### Loss to follow-up

• For the primary outcome (ie death of trial patients) there should be minimal loss as patient death will be automatically flagged via the Office of National Statistics

• For secondary outcome measures around 5% of patients may be lost to follow-up due to non-compliance with questionnaires or movement to other areas. Study co-ordinators at each centre will maintain telephone contact with participants to record Health Service Resource Use, to record adverse events, to alert them of the questionnaires' arrival, to ensure addresses are current and to follow-up any non-responders.

### Statistical issues

#### Type of analyses

The trial data will be analysed on an intention-to-treat basis with patients included in the groups assigned at randomisation, irrespective of future management and events. Outcome measure event tracking will begin at randomisation and continue until death or the end of follow-up. Analysis of time to event data will use log rank tests and possibly other methods suitable for survival data, in particular to take account of known prognostic variables.

#### Frequency of analyses

A limited number of interim analyses will be performed by the trial statistician as specified by the Data Monitoring Committee (DMC). The accumulating results will not be available to the trialists or other principal investigators. The final, definitive analysis of the trial data will be conducted 120 months after the date of commencement of the trial.

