**Methods/Design:**

Twenty centres in the UK, Australia, Poland and Brazil are planning to randomise 3000 coronary artery bypass graft surgery patients to single or bilateral internal mammary artery grafting. Supplemental grafts may be either saphenous vein or radial artery. Coronary artery bypass grafting can be performed as an on-pump or off-pump procedure. The primary outcome is survival at 10 years and secondary end-points include clinical events, quality of life and cost effectiveness. The effect of age, left ventricular function, diabetes, number of grafts, vein grafts and off-pump surgery are pre-specified subgroups.

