### Centres

#### Study sites

The list of participating centres is given in Table 3. Each centre will be paid a pro-rata sum of 1.0 FTE for years 1–2, 0.5 FTE for year 3 and 0.2 FTE for years 4–10, to help support a study co-ordinator.

Study site co-ordinators will be responsible for screening patients (and recording the data on a screening log), enrolling patients into the trial, providing a contact point for patients, liasing with CTEU, completing CRFs, ensuring annual questionnaires are sent and processed, recording adverse events, ensuring forms are sent to CTEU and that all edit queries are resolved.

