### Proposed timetable for ART study

Jun 2004 Grant awarded by MRC & BHF - Recruitment starts

Jun 2007 Recruitment completed

2009 First patient completes 5 years

2012 Last patient completes 5 years  - Analysis and publication of 5 year data

2014 First patient completes 10 years

2017 Last patient completes 10 years

2017/8 Publication of 10 year data

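### The definitive analysis is dated 120 months from trial start (June 2014), which contradicts the protocol's own timetable and its 10-year primary outcome, and falls short of the stated 90% power if followed literally

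*Protocol article*

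**What the plan says.** All references are to the protocol article.

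- **Frequency of analyses:** "The final, definitive analysis of the trial data will be conducted 120 months after the date of commencement of the trial".
- **Proposed timetable:** recruitment opens in June 2004 and closes in June 2007. The first patient reaches ten years in 2014. For the end of follow-up it gives "2017 Last patient completes 10 years", with the ten-year results published in 2017/8. The five-year analysis is placed in 2012, when the last recruit has five years.
- **Abstract, Methods/Design:** "The primary outcome is survival at 10 years".
- **Number of patients:** the design difference is 25% against 20% mortality at ten years, which "with 90% power at 5% alpha requires 2928 patients". Enrolment is described as follows: "The aim is to enrol at least 3000 patients (1500 in each arm) over a 2 to 3 year recruitment period".
- **Follow-up, Tables 1 and 2:** each participant is contacted yearly through year 10, and SF-36 is collected before surgery and at years 5 and 10.
- **Type of analyses:** time-to-event data are compared with log-rank tests.
- **Study sites:** co-ordinator funding is 1.0 FTE for the first two years, then "0.5 FTE for year 3 and 0.2 FTE for years 4–10".

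**The concern.** The article gives two incompatible dates for its main analysis, about three years apart. Counted from June 2004, 120 months ends in June 2014, the year in which the timetable has only the first patient reaching ten years.

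If the sentence were followed:

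- Patients would have 7 to 10 years of follow-up, and almost nobody would be at risk at year 10, the time point that defines the primary outcome.
- There would be fewer deaths than the sample size assumes.
- The year-10 questionnaires, including one of only two post-operative SF-36 assessments, would be missing for nearly everyone.
- Much of the follow-up beyond year 7 would be lost. The Background cites the authors of one observational study, who expected the benefit to grow with longer follow-up because vein graft failure rises after about seven years.

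**Working it through.** **1. Dates.** June 2004 + 120 months = June 2014. A patient randomised in June 2007 then has 7 years of follow-up and one randomised in June 2004 has 10. Under uniform accrual the mean is 8.5 years. Counting 120 months from the close of recruitment (June 2007) gives June 2017, which agrees with the timetable.

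**2. The plan's own sample size.** Inputs from Number of patients: p1 = 0.25, p2 = 0.20, power 90%, alpha 5% (taken as two-sided). The mean proportion is 0.225.

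n per arm = [1.960 × √(2 × 0.225 × 0.775) + 1.2816 × √(0.25 × 0.75 + 0.20 × 0.80)]² / 0.05² = (1.1575 + 0.7555)² / 0.0025 ≈ 1464

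The total is 2928, an exact match. The figure therefore assumes that ten-year mortality is observed in every patient.

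**3. Full follow-up, 3000 patients.** Deaths = 1500 × (0.25 + 0.20) = 675. Under proportional hazards HR = ln(0.80)/ln(0.75) = 0.776, so |ln HR| = 0.254. Schoenfeld power is Φ(√D × |ln HR| / 2 − 1.960). With D = 675 this is Φ(3.300 − 1.960) = 91.0%.

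**4. Cut at 120 months.** Assume constant hazards h = −ln(1 − p)/10, uniform accrual over R years and no loss to follow-up. The expected proportion dead in an arm is

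1 − [e^(−(10−R)h) − e^(−10h)] / (R × h)

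For R = 3:

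- SIMA, h = 0.02877: 1 − (0.8176 − 0.75)/0.0863 = 0.2167
- BIMA, h = 0.02231: 1 − (0.8554 − 0.80)/0.0669 = 0.1726
- Deaths = 1500 × (0.2167 + 0.1726) ≈ 584
- Power = Φ(3.069 − 1.960) = 86.6%

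| Analysis, N = 3000 | Follow-up (years) | Deaths | Power |
|---|---|---|---|
| All followed to 10 years | 10 | 675 | 91.0% |
| 120 months, 2-year accrual | 8–10 | 615 | 88.3% |
| 120 months, 3-year accrual | 7–10 | 584 | 86.6% |

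With 2928 patients the two early-cut figures are 87.5% (2-year) and 85.8% (3-year). Reaching 90% at the early cut would need about 3180 patients (2-year) or 3350 (3-year).

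**5. Sensitivity (assumptions not in the protocol; N = 3000, 3-year accrual, cut at 120 months).**

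- Weibull hazards with the same ten-year mortality: shape 0.7 gives 88.0%, shape 1.5 gives 84.2%, shape 2.0 gives 81.7%.
- No benefit until a given year, then enough to reach 20% at year 10 (simulated log-rank test, 1500 replicates, simulation error about 1 point):

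| Benefit starts after | HR thereafter | Cut at 120 months | Full 10 years |
|---|---|---|---|
| 2 years | 0.72 | 79% | 87% |
| 4 years | 0.63 | 70% | 87% |
| 5 years | 0.55 | 65% | 87% |

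**The case against.** The strongest defence is that the 120-month sentence is a slip. The timetable, the follow-up schedule and the stated primary outcome all point to 2017, and the timetable places the five-year analysis when the last recruit has five years. That reading is plausible, and it means that one should not infer a settled plan to analyse early. It does not remove the fault: the statistical section gives an explicit date for the definitive analysis, and that date is wrong against everything around it.

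A reader might go further in three ways that the document does not support.

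- **That the primary outcome could not be analysed in June 2014.** The planned log-rank test handles staggered censoring, and about 584 deaths would be expected.
- **That power would collapse.** Under proportional hazards the shortfall against the stated 90% is 3.4 points with 3-year accrual and 1.7 points with 2-year accrual; the article allows either with "over a 2 to 3 year recruitment period". The much lower figures need an assumed delay in benefit. Deferring all benefit to year 7 would require a hazard ratio of about 0.25 thereafter: (0.2231 − 0.7 × 0.2877)/3 divided by 0.02877. The article's own evidence is a pooled hazard ratio of 0.81, and one study with a lower combined event rate by six years (p = 0.06). That suggests a benefit that may grow, not one that is absent until late.
- **That site support ends before late recruits finish.** The funding sentence does not say whether its years run from trial start, centre start or randomisation. UK deaths are in any case flagged through national statistics.

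**Conclusion.** The point holds as an internal contradiction about the date of the definitive analysis. June 2014 cannot be reconciled with a ten-year outcome in patients recruited until June 2007, nor with a sample size that reproduces exactly only when all patients have ten years of observation. Followed literally, the early date costs about 91 expected deaths (675 − 584, or 13%) and 4.4 points of power (91.0% to 86.6%) with 3-year accrual. With 2-year accrual the cost is about 60 deaths and 2.7 points (91.0% to 88.3%).

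These figures assume 3000 patients, uniform accrual, constant proportional hazards, two-sided 5% alpha and no loss to follow-up for death. The loss grows if mortality or benefit is concentrated late, but its size then depends on assumptions that the article does not make. The power loss is modest on the central assumptions. The correction is still needed, because the sentence governs the primary analysis and would leave the ten-year comparison incomplete.

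**What to change.** Amend the sentence under Frequency of analyses so that the final analysis takes place when the last randomised patient has completed ten years, about June 2017 on the stated timetable. Tying it to the last patient rather than to a calendar count also keeps it right if recruitment runs shorter or longer than planned. On the assumptions above, power is then about 91% with 3000 patients.

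Under Study sites, state from what date years 4 to 10 are counted, and whether the funding covers the yearly contacts of late recruits until the final analysis.

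The first change is one sentence and matches the existing timetable, so it adds no patients and no delay to the planned 2017/8 publication. The second is a clarification. It has a cost only if the years turn out to run from trial start, in which case low-level site support would be needed for about three further years.
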